### Sample size

The principle endpoint is post intervention (4 weeks). Our previous RCT
demonstrated that stroke survivors using the SMART Arm alone or with electrical
stimulation demonstrated significant improvements in MAS-6 scores compared to
the control group [16]. On this basis, we estimate a mean improvement of 1.8 (SD 2) in the
usual therapy group, 2.91 (SD 2) in the SMART Arm alone group and 3.91 (SD 2) in
the SMART Arm with OT-stim group. To achieve 80% power and a significance of
0.05 with pairwise comparisons, 22 subjects are required per group, to total 66
subjects. A 15% dropout rate will be allowed to account for withdrawals, thus 25
subjects will be recruited per group, totalling 75.

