**Figure 1 F1:**
[figure not shown]
SMART Arm.

To date, a 12-hour SMART Arm training program with or without electromyographic
(EMG)-triggered electrical stimulation to triceps has been investigated in chronic
stroke survivors with severe upper limb disability. Compared with the control group,
those who underwent SMART Arm training with or without stimulation showed a
significant improvement in upper limb function (improvement in MAS6 item 6 score)
that was sustained at 2 months follow-up [16], an improved ratio of triceps to biceps EMG activity during reaching [17], and greater corticospinal reactivity [18]. There were however, variations in the expression of additional benefits
derived from the use of EMG-triggered electrical stimulation. As this may have been
due to the use, by some individuals, of maladaptive patterns of EMG activity such as
co-contraction of biceps and triceps, that could nonetheless trigger stimulation, a
new method of outcome-triggered electrical stimulation (OT-stim) was developed.
Here, electrical stimulation is triggered when initial goal directed motion
surpasses an individualised threshold. Thus, assistance by means of electrical
stimulation (and reinforcement) occurs when the movement generated voluntarily is
commensurate with the desired outcome. In a pilot trial of SMART Arm with OT-stim
during inpatient rehabilitation, SMART Arm training (with or without OT-stim), led
to a significantly greater improvement in upper limb function as compared to usual
therapy alone [19]. In that these improvements were evident early after stroke, further
investigation within the context of a larger trial is warranted [20].

Thus, the primary aim of the current randomised controlled trial (RCT) is to
determine the ability of SMART Arm training with or without OT-stim compared to
usual therapy to improve upper limb function in stroke survivors with severe upper
limb disability undergoing inpatient rehabilitation. In addition, we will determine
the impact of the different training programs on upper limb impairment, activity and
participation.

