### Population

All stroke survivors admitted to the Acute Stroke Unit at each hospital will be
screened for eligibility. Participants will be eligible if they are adult stroke
survivors (>17 years) with a primary diagnosis of first-ever unilateral
stroke (ischaemic or haemorrhagic, including subarachnoid haemorrhage) less than
four months previously, which has been confirmed either radiographically (CT or
MRI) or clinically by the consulting physician; demonstrate severe upper limb
disability equivalent to a score of three or fewer out of a possible six points
(inability to hold the upper limb in position when placed at 90° shoulder
flexion in sitting) on the MAS item six; and are able to follow single-stage
commands, either with verbal instructions, demonstration or other non-verbal
cues.

Participants will be excluded if they are medically unstable as defined by the
medical registrar or by location in an acute medical ward; have upper limb
comorbidities that could limit their functional recovery (e.g., arthritis, pain,
other neurological disorders); have a contraindication to the use of (e.g.,
pacemaker insitu), or inability to tolerate, electrical stimulation (e.g.,
hypersensitivity or skin condition); have an infectious disease requiring the
use of personal protective equipment (e.g., methicillin resistant staphylococcus
aureus or vancomycin resistant enterococcus) or are unable to sit without
support.

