#### Primary outcome measure

The primary outcome measure will be performance on the MAS item 6 at the post
intervention time period (4 weeks). The MAS is designed to measure recovery
of the affected limb over 3 task-related subscales (upper arm function, hand
and advanced hand movements) that are scored from 0–6. It is the
stroke recovery scale most commonly used in clinical practice in Australia
and takes less than 10 minutes to complete. The reliability and validity of
this measure with the stroke population has been previously documented [27]. It has been shown to be sensitive to change in performance in
people with severe upper limb disability after training with SMART Arm [16,19].

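### At 22 per group the protocol's own gains give 80% power for only one of the three pairwise comparisons, and that one rests on a 1.0-point stimulation increment with no source shown

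*Protocol article*

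**What the plan says.** The primary outcome is MAS item 6 at 4 weeks. The Primary outcome measure section describes the MAS upper-limb subscales as "and advanced hand movements) that are scored from 0–6". The Population section requires "disability equivalent to a score of three or fewer out of a possible six points" at entry. No mean or distribution of baseline scores is given.

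The Sample size section refers to the group's previous RCT, in which SMART Arm with or without stimulation improved more than control. For the arm without the device it says: "On this basis, we estimate a mean improvement of 1.8 (SD 2) in the". The gains for the two device arms come next: "usual therapy group, 2.91 (SD 2) in the SMART Arm alone group and 3.91 (SD 2) in", where the last figure belongs to OT-stim. The claim then begins "To achieve 80% power and a significance of" 0.05 and concludes that, for pairwise comparisons, 22 per group (66 in total) are required, raised to 25 per group (75) for 15% dropout. Sidedness and multiplicity adjustment are not stated.

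The Background describes the previous trial as a 12-hour programme in chronic stroke with EMG-triggered stimulation. On what stimulation added, it says: "There were however, variations in the expression of additional benefits". It suggests this may have been "due to the use, by some individuals, of maladaptive patterns of EMG activity such as" co-contraction, and gives that as the reason for developing OT-stim. The inpatient pilot is reported for both SMART Arm groups together: "during inpatient rehabilitation, SMART Arm training (with or without OT-stim), led" to greater improvement than usual therapy.

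**The concern.** The power statement covers pairwise comparisons in general, but the three assumed gains imply very different contrasts: 2.11, 1.11 and 1.00 points. One sample size cannot give about 80% power for all three. The two smaller contrasts carry real aims. One asks whether the device without stimulation beats usual therapy; the other asks what stimulation adds, which the Discussion says the trial will allow to be assessed.

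Two features of the inputs add to this. The largest contrast includes a full point for stimulation that neither the cited trial, as described, nor the pilot, as described, is shown to support. The assumed gain for the OT-stim arm also lies close to what the scale permits for people entering at 2, and beyond it for people entering at 3.

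At stake is how a null result is read. A non-significant difference between the two SMART Arm groups, or between SMART Arm alone and usual therapy, could be taken as evidence of no effect from a trial described as having 80% power, when it had well under half.

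**Working it through.** **Inputs.** Gains 1.8, 2.91 and 3.91, SD 2 in each arm, alpha 0.05, 22 per group (Sample size); scale 0–6 (Primary outcome measure); entry at 3 or less (Population). Assumed here: two-sided two-sample t-test on gains; Bonferroni, where shown, uses 0.05/3 = 0.0167.

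**1. Reproducing 22 per group.** For 3.91 − 1.8 = 2.11 with SD 2, 80% power needs 16 per group unadjusted and 21 with Bonferroni. Dividing 21 by 0.955, the efficiency of a rank test, gives 22. So 22 is recovered to within one patient, but only for the largest contrast and only with a multiplicity adjustment.

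**2. Power for each contrast at 22 per group.** The standard error of a difference is 2 × √(2/22) = 0.603. The noncentrality is the difference divided by 0.603, with 42 degrees of freedom.

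| Contrast | Difference | Noncentrality | Power, unadjusted | Power, Bonferroni | n per group for 80%, unadjusted |
|---|---|---|---|---|---|
| OT-stim vs usual | 2.11 | 3.50 | 93% | 84% | 16 |
| SMART Arm alone vs usual | 1.11 | 1.84 | 44% | 27% | 52 |
| OT-stim vs SMART Arm alone | 1.00 | 1.66 | 37% | 21% | 64 |

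If all 25 recruited per group were analysed, the two smaller contrasts would reach only 48.5% and 41%, unadjusted.

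**3. Dependence on the stimulation increment.** The increment is 3.91 − 2.91 = 1.00. Writing the OT-stim versus usual difference as 1.11 plus the increment, unadjusted power at 22 per group is:

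| Increment | Difference | Power |
|---|---|---|
| 1.00 | 2.11 | 93% |
| 0.75 | 1.86 | 85% |
| 0.50 | 1.61 | 74% |
| 0.25 | 1.36 | 60% |
| 0 | 1.11 | 44% |

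**4. Whether 3.91 with SD 2 can occur on the scale.** The largest possible gain is 6 minus baseline: 6, 5, 4 or 3 points for entry at 0, 1, 2 or 3. For a group all entering at score b, with worsening allowed, the largest SD compatible with a mean gain of 3.91 is √[(6 − b − 3.91)(3.91 + b)]:

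- b = 0: √(2.09 × 3.91) = 2.86
- b = 1: √(1.09 × 4.91) = 2.31
- b = 2: √(0.09 × 5.91) = 0.73
- b = 3: a mean of 3.91 is impossible, since nobody can gain more than 3

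For mixed baselines, a linear programme over all combinations of entry score and gain gives the highest mean baseline at which mean 3.91 and SD 2 can both hold: 1.74 if nobody worsens, 1.86 if worsening is allowed. At the 1.74 limit the outcomes are all-or-nothing: about 42% enter at 0 and reach 6, 46% enter at 3 and reach 6, and 12% enter at 3 and do not change.

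**5. Size of a ceiling effect, if the gains are latent.** Assumption: normal gains with SD 2 are added to baseline, rounded and cut at 0 and 6. With baseline spread evenly over 0–3, mean gains become 1.74, 2.60 and 3.27. OT-stim versus SMART Arm alone falls to 0.67 (power 29%). OT-stim versus usual falls to 1.53, but the SD falls too, to about 1.6, so power is 88% unadjusted and 76% with Bonferroni. From everyone entering at 0 to everyone entering at 3, power for OT-stim versus usual runs from about 93% down to 81% unadjusted, and from about 84% down to 67% with Bonferroni.

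**The case against.** A reader might infer that 3.91 with SD 2 cannot occur on this scale, or that the ceiling alone shows the 80% to be overstated. The documents support neither. The Population section sets only an upper limit for entry, no baseline mean is given, and the Background describes a device for people with little or no muscle activity, which is compatible with low entry scores. At a mean baseline below about 1.7 the figures are attainable.

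A stated mean improvement is also most naturally read as the gain expected to be observed, with any ceiling already in it. Cutting it again at 6, as in step 5, would then count the ceiling twice, and SD 2 might even be conservative. Even on the latent reading, OT-stim versus usual therapy keeps at least 81% unadjusted power. Step 5 therefore shows sensitivity, not an error.

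On the increment, the cited trial is not at hand, so its results by arm cannot be judged. The Background gives a reason to expect more from OT-stim than from EMG-triggered stimulation, and the section says the gains are estimates. The pilot may have informed them without being cited there. All of that stands. What remains is that the article presents the gains as following from the earlier trial, while its own account of that trial, and of the pilot, contains no stimulation increment.

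None of this touches step 2, which uses only the protocol's own figures.

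**Conclusion.** The concern holds in this form: the 80% power stated for pairwise comparisons is correct for one contrast in three. On the protocol's own gains it is 93% (84% with Bonferroni) for OT-stim versus usual therapy, about 44% for SMART Arm alone versus usual therapy, and about 37% for OT-stim versus SMART Arm alone. These figures assume a two-sided t-test on gains; a one-sided test at 0.05 gives about 57% and 50% for the two smaller contrasts, still well short of 80%.

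The adequacy of the one well-powered contrast depends on an assumed 1.0-point increment whose source is not shown. With no increment its power is about 44%. That is a risk from an unsupported input, not proof that the increment is wrong.

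The scale limit is secondary. The OT-stim gain requires a low mean baseline (about 1.7 to 1.9 at most) that the section does not state, and its effect on power is conditional on that baseline and on how the gains are read.

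**What to change.** In the Sample size section:

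- State the assumed mix of baseline MAS item 6 scores, and say whether the gains are expected observed values.
- Restate power at 22 per group for each of the three contrasts, on gains that respect the 0–6 range, giving sidedness and any multiplicity adjustment.
- State that the 1.0-point stimulation increment is an assumption, and show power over increments from 0 to 1.0 point.
- Describe OT-stim versus SMART Arm alone as estimation with a confidence interval, not as a comparison with 80% power. With SD 2 and 22 per group, the expected 95% half-width is about 2.018 × 0.603 = 1.2 points, wider than the assumed 1.0-point difference.
- Drop the 80% statement for SMART Arm alone versus usual therapy as well, and give its actual power.

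The cost is a short calculation and revised wording. No extra patients are needed. The downside is that the stated power becomes less favourable for two of the three contrasts, and openly conditional for the third.

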### Randomisation and blinding

All participants will provide written informed consent. In the event that a
participant is unable to provide informed consent, consent will be sought from
their legal guardian. After completion of the initial assessment, participants
will be randomised to one of three dose-matched groups (two intervention and one
control). The intervention groups are SMART Arm training *with* OT-stim
(SMART Arm OT-stim) and usual therapy; SMART Arm training *without*
OT-stim (SMART Arm alone) and usual therapy. The control group will receive
usual therapy only. Concealed randomisation will be prepared by an offsite
investigator, not involved in recruitment, intervention or data collection,
using a computer generated random number sequence. Consecutively numbered,
randomly ordered opaque envelopes containing group allocation in permuted blocks
of four or six in a 1:1 ratio will be opened consecutively after baseline
assessment in the presence of the participant. Usual therapists will be informed
of group allocation.

Research assistants who enrol participants, and conduct pre, post and follow-up
assessments will be blinded to group allocation throughout the study.
Participant coding will not refer to group allocation and participants will be
instructed not to divulge information regarding their intervention to the
assessors during assessment. Participants, SMART Arm trainers and usual
therapists (physiotherapy and occupational therapy) will not be blinded to group
allocation. To control expectancy effects for participants and usual therapists,
it will be explained that it is not yet determined which therapy is more
effective.

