### Data analysis

Data analysis will be performed on an intention-to-treat basis using an alpha
level of 0.05. Descriptive statistics will be used to ensure comparability of
scores between groups at baseline, to describe performance at each phase and to
test whether the assumptions for use of parametric statistics have been met. If
the assumptions for F or t-tests are violated, equivalent non-parametric
statistics will be utilized. The main hypothesis will be tested using mixed
effects models, in a 3 group (SMART Arm + OT stim, SMART Arm alone, usual
therapy) × 4 phase (0, 4, 26, 52 weeks) model. This will be followed by
between-groups planned comparisons. All secondary outcomes will be analysed in a
similar manner.

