## Discussion

This will be the first prospective trial to compare the effect of dose-matched
volumes of SMART Arm with OT-stim and usual therapy, versus SMART Arm alone with
usual therapy versus usual therapy alone during inpatient rehabilitation following
stroke. While it is known that intensive and repetitive, task-oriented training is
critical to drive motor recovery after stroke [39,40], those with severe impairment and ‘not enough movement to work
with’ require assistance to complete a functional movement pattern. Currently,
the most commonly used method is manual assistance by a therapist. The minimal time
spent on the upper limb during physiotherapy indicates however, that this
time-inefficient strategy is not prioritised. It is likely that gait training
requirements, which are paramount to determining discharge destination, are
prioritised. Another option is robotic therapy, however availability is currently
limited and functional outcomes remain inconclusive [8,41,42].

In the event that SMART Arm training, with or without electrical stimulation, leads
to demonstratable significant improvements in upper limb function, reduced
impairments or increased participation, an alternative option for retraining would
be presented. Improvements in impairments and activity using the SMART Arm have been
obtained in chronic stroke survivors [16], and the indications from our pilot work are that similar outcomes may be
achieved in those undertaking inpatient rehabilitation [19]. If positive changes may be induced during inpatient rehabilitation, this
may allow some stroke survivors to regain levels of function that are sufficient to
enable progression to interventions such as constraint induced movement therapy.

This study will also allow the impact of augmenting training with electrical
stimulation to be assessed in the context of severe motor disability. This will be
the first large study to determine the effect of outcome-triggered stimulation, in
circumstances in which the stroke survivor is *rewarded* for performing the
desired movement, rather than for simply generating sufficient levels of EMG i.e.
regardless of the functional consequences.

Findings from this study will provide insights into the effects of practice on
regaining motor skill in those with severe upper limb disability following stroke.
The collection of detailed training data will generate new knowledge regarding the

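### The 80% power claimed for pairwise comparisons at 22 per group holds for only one of the three contrasts; the other two have about 44% and 37%

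*Protocol article*

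**What the plan says.** The Sample size section names 4 weeks as the principal endpoint. It gives the assumed gain for the control arm first: "we estimate a mean improvement of 1.8 (SD 2) in the". The assumed gains for the two device arms come next: "usual therapy group, 2.91 (SD 2) in the SMART Arm alone group and 3.91 (SD 2) in". The last of these figures belongs to the OT-stim arm. The result rests on these inputs and is stated as "0.05 with pairwise comparisons, 22 subjects are required per group, to total 66", with 80% as the target power. Recruitment is then set at 25 per group to allow for 15% dropout. The section does not say which pairwise comparison the 80% refers to, whether the test is one- or two-sided, or whether alpha is split.

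The Data analysis section also works with a single alpha, 0.05, and mentions no division of it: "Data analysis will be performed on an intention-to-treat basis using an alpha". It tests the main hypothesis in a model with three groups and four time points, followed by planned comparisons between groups. The Background gives the primary aim as SMART Arm training, with or without OT-stim, against usual therapy. The Discussion adds a further question, what the stimulation itself contributes: "This study will also allow the impact of augmenting training with electrical".

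**The concern.** The sentence speaks of pairwise comparisons in the plural and singles none out, so a reader will take 80% to apply to each. The assumed means are almost evenly spaced. The outer pair therefore differs by about twice as much as either adjacent pair, and one group size cannot give all three contrasts similar power.

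The two adjacent contrasts matter. SMART Arm alone versus usual therapy falls within the primary aim if that aim means each SMART Arm group against control. OT-stim versus SMART Arm alone is the stimulation question raised in the Discussion. If their power is well below 80%, a non-significant result on either would carry little information, while the stated 80% would invite a reader to see it as evidence against an effect.

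**Working it through.** **Inputs.** From the Sample size section: mean gains 1.8, 2.91 and 3.91; SD 2 in each group; alpha 0.05; target power 80%; 22 per group. Allocation is equal (Randomisation and blinding section). Two-sided testing is my assumption. The SD is given for the improvement itself, so any precision gained by using change scores is already counted.

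**Differences.**
- OT-stim vs usual therapy: 3.91 − 1.80 = 2.11
- SMART Arm alone vs usual therapy: 2.91 − 1.80 = 1.11
- OT-stim vs SMART Arm alone: 3.91 − 2.91 = 1.00

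**Reproducing the 22.** The normal approximation is n per group = 2 × SD² × (1.960 + 0.842)² / difference², which is about 62.8 / difference² here.
- 2.11: 62.8 / 4.452 = 14.1, so 15 (noncentral t: 16)
- 1.11: 62.8 / 1.232 = 51.0, so 51 (noncentral t: 52)
- 1.00: 62.8 / 1.000 = 62.8, so 63 (noncentral t: 64)

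None of these is 22. The nearest pairwise route is the largest difference with an unstated Bonferroni alpha of 0.05/3, which gives 20.3, so 21 per group. An overall three-group F test needs 19 per group, but it is not a pairwise comparison. No variant tried gives 22 for a difference of 1.11 or 1.00. The smallest requirement found for these, at one-sided 0.05, is 41 and about 50 per group.

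**Power at 22 per group.** The standard error of a difference is 2 × √(2/22) = 0.603. The noncentrality parameters are 2.11/0.603 = 3.50, 1.11/0.603 = 1.84 and 1.00/0.603 = 1.66. The two-sided 5% critical value of t on 42 degrees of freedom is 2.02, already above the last two.

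| Contrast | Difference | Two-sided 0.05 | Bonferroni 0.05/3 | One-sided 0.05 | Two-sided 0.05, 25 per group |
|---|---|---|---|---|---|
| OT-stim vs usual therapy | 2.11 | 93% | 84% | 96% | 95% |
| SMART Arm alone vs usual therapy | 1.11 | 44% | 27% | 57% | 49% |
| OT-stim vs SMART Arm alone | 1.00 | 37% | 21% | 49% | 41% |

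Using the error variance pooled over all three groups (63 degrees of freedom) leaves the two-sided figures at 93%, 44% and 37%.

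**Detectable difference.** At 22 per group, two-sided 0.05 and SD 2, 80% power is reached at a difference of 1.73 points. Two of the three assumed differences lie below it. For 80% power at 22 per group, the SD would have to fall from 2 to about 1.28 for the 1.11 contrast, or about 1.16 for the 1.00 contrast.

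**Joint results.** Simulation under the plan's assumptions, with unadjusted two-sided tests at 0.05, gives about a 43% chance that both SMART Arm groups beat usual therapy and about a 9% chance that all three contrasts are significant.

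**The case against.** The best defence is that 22 per group was meant for the largest contrast with some allowance for multiplicity. That does come close: 21 per group are needed and power at 22 is 84%. But the section neither restricts the claim to that contrast nor mentions an adjustment, so the sentence is still wrong as a statement about pairwise comparisons. Nor can the mixed model be assumed to close the gap, since the SD is already that of the improvement and the article claims no further reduction.

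A second defence is that the contrasts are not equally important. This stands in part. The primary aim is set against usual therapy, and the stimulation comparison is not named there. The 44% figure is therefore the more serious one.

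Three stronger readings are tempting and should not be drawn:
- *The primary aim is a pooled SMART Arm contrast, so the plan tests the wrong thing.* The Background wording can equally mean each SMART Arm group against control, and the article nowhere mentions pooling.
- *The assumed 1.0-point stimulation benefit is unjustified, because the Background says of the earlier trial:* "There were however, variations in the expression of additional benefits". The same paragraph offers a possible explanation (maladaptive muscle activity that could still trigger stimulation), says OT-stim was developed in response, and reports an inpatient pilot using it. Whether 1.0 point is optimistic depends on sources not available here.
- *Both smaller contrasts will more likely than not fail.* This holds for two-sided testing. At one-sided 0.05 the 1.11 contrast has 57% power, still short of 80%.

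The article also does not itself plan to read a null result as no effect. That risk lies with the reader.

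**Conclusion.** The power statement is wrong as written. On the section's own means and SD, 80% power is met only for OT-stim versus usual therapy. The other two contrasts have roughly half the stated power. The exact percentages rest on two-sided t-tests at 0.05 and 22 evaluable participants per group. The conclusion that both smaller contrasts fall short of 80% does not: it also holds one-sided, with Bonferroni, with a pooled error term, and with all 25 per group retained. The finding concerns the stated power. It does not show that the assumed effects are wrong or that the trial must be enlarged.

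**What to change.** Replace the power sentence with one figure per contrast, for example: with 22 evaluable participants per group, SD 2 and a two-sided test at 0.05, power is 93% for OT-stim versus usual therapy (difference 2.11), 44% for SMART Arm alone versus usual therapy (1.11) and 37% for OT-stim versus SMART Arm alone (1.00). State the sidedness and whether alpha is adjusted; if a three-way Bonferroni correction is intended, the figures are 84%, 27% and 21%. Commit to reporting each pairwise contrast with its 95% confidence interval, and state that a non-significant result for either low-powered contrast will not be read as no effect. The cost is wording only, with no extra participants and a less favourable stated power for two contrasts.

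Optionally, the sponsor could name pooled SMART Arm versus usual therapy at 4 weeks as the primary contrast. The difference would be (2.91 + 3.91)/2 − 1.80 = 1.61, and with 44 versus 22 participants power is about 86%. This is a design choice that the stated aim does not require. It changes the primary hypothesis test and averages two groups that the plan expects to differ by 1 point, so it is more than a wording change.

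### Recruiting 25 per group does not cover 15% dropout: about 21 per group would remain, against the 22 the protocol requires

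*Protocol article*

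**What the plan says.** The Sample size section names the 4-week assessment as the endpoint on which the trial is sized. It assumes mean improvements on MAS item 6 of 1.8 (usual therapy), 2.91 (SMART Arm alone) and 3.91 (SMART Arm with OT-stim), each with SD 2. For 80% power it states the requirement as "0.05 with pairwise comparisons, 22 subjects are required per group, to total 66". It then makes the allowance for loss: "subjects. A 15% dropout rate will be allowed to account for withdrawals, thus 25" — and concludes that this many "subjects will be recruited per group, totalling 75".

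The Abstract and the Design section repeat the total of 75. No section gives the inflation formula, or says whether the 15% refers to loss by 4 weeks or over the 52 weeks of follow-up.

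**The concern.** The protocol presents 25 as the consequence of two stated figures, 22 required and 15% lost. A dropout rate is a fraction of those recruited, so the required number must be divided by the fraction retained. Multiplying the required number by one plus the rate gives too few, and rounding that product down makes the gap a little larger.

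At stake is whether the headline figure of 75 does what readers are told it does. If dropout runs exactly at the planned rate, the trial finishes below its own stated requirement.

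**Working it through.** **Inputs, all from the Sample size section:** required 22 per group (66 total); dropout 15%; recruited 25 per group (75 total).

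**Reproducing the stated 25.** The protocol gives no formula, so the route is inferred:
- Required × (1 + rate): 22 × 1.15 = 25.3. Only rounding down gives 25, and 3 × 25 = 75.
- The same product rounded up gives 26 per group. Applied to the total, 66 × 1.15 = 75.9, which rounds up to 76.
- None of the usual calculations gives 25 and 75 if sample sizes are rounded up.

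**What 25 per group delivers at 15% loss:**
- Per group: 25 × (1 − 0.15) = 21.25, below 22.
- Total: 75 × (1 − 0.15) = 63.75, below 66.
- Largest loss that still leaves 22: 1 − 22/25 = 0.12, i.e. 12%.

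**What 15% loss requires:**
- Per group: 22/(1 − 0.15) = 25.88, so 26.
- Total: 3 × 26 = 78.
- Check: 26 × 0.85 = 22.1 and 78 × 0.85 = 66.3, which meet 22 and 66.
- Shortfall: 26 − 25 = 1 per group and 78 − 75 = 3 overall (3/75 = 4%).

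**Effect on power.** The differences follow from the assumed means: 3.91 − 1.8 = 2.11; 2.91 − 1.8 = 1.11; 3.91 − 2.91 = 1.00. The SD is 2 in every group. The protocol sets alpha at 0.05 without stating sidedness; two-sided is assumed, with a two-sample t-test and no multiplicity adjustment.

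| Comparison | Difference | Power at 22 per group | Power at 21.25 | Power at 21 |
|---|---|---|---|---|
| OT-stim vs usual therapy | 2.11 | 92.8% | 91.9% | 91.6% |
| SMART Arm alone vs usual therapy | 1.11 | 43.6% | 42.3% | 41.9% |
| OT-stim vs SMART Arm alone | 1.00 | 36.7% | 35.6% | 35.3% |

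The dropout step therefore costs about one percentage point per comparison at 21.25 per group, and between one and two points at 21.

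**Does the shortfall cross the 80% line anywhere?** No. On the same test, the 2.11 contrast needs 16 per group at 0.05, or 21 per group at 0.05/3, so it keeps 80% power with 21. The 1.11 and 1.00 contrasts need 52 and 64 per group at 0.05. They fall well short at 22 as well as at 21, so dropout is not the cause.

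**The case against.** The strongest objection concerns timing. The sample size is set for the 4-week endpoint, but follow-up runs to 52 weeks, and the allowance is for withdrawals with no time attached. If 15% is meant as loss over the year, loss by 4 weeks could be 12% or less and 22 per group would still be reached. The Intervention section also lets participants who miss sessions make up the days, which may help retention. This is a fair limit on the claim that the target will be missed in practice. It does not rescue the sentence, which attaches the 15% directly to the 22 needed at 4 weeks. If a 52-week rate was intended, the text has to say so.

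A second objection is that the Data analysis section plans intention-to-treat with a mixed effects model over all four assessments, so people who leave after 4 weeks still contribute to the primary time point. That is right. However, someone lost before 4 weeks adds little information on the 4-week effect, and the protocol itself chose to inflate for withdrawals.

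The third objection is size: one participant per group and a point or two of power. That stands, and it is why the correction proposed is to the wording rather than to recruitment. It is also true that correcting this step alone does not give 80% power for every pairwise comparison.

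**Conclusion.** The statement is wrong as written. On the protocol's own figures, 25 per group absorbs 12% loss; at 15% it leaves 21.25 per group and 63.75 overall, against the required 22 and 66. The matching target is 26 per group, 78 in total.

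The arithmetic needs no outside figure. Expecting fewer than 22 per group at the primary endpoint also assumes that the full 15% is lost before the 4-week assessment, which is the plain reading of the section but is not spelled out. The power figures assume two-sided, unadjusted t-tests. The practical effect is small, and no comparison moves from above 80% power to below it.

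**What to change.** Keep 75 and correct the sentence, for example: 75 participants (25 per group) allow for 12% dropout at the 4-week endpoint; at 15% dropout about 21 per group are expected, giving power of about 92%, 42% and 35% for differences of 2.11, 1.11 and 1.00 points respectively. State that the rate refers to 4 weeks or, if it was meant to cover 52 weeks, say so and give the loss expected by 4 weeks.

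If the sponsor prefers to keep the 15% allowance, change the target to 26 per group and 78 in total, and update the Abstract and the Design section to match.

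The first option enrols no one extra. It costs one sentence and a slightly less favourable stated allowance. Quoting these powers will show that they conflict with the claim of 80% power for pairwise comparisons, so that claim should be reviewed at the same time. If the base figure of 22 is revised, divide the new figure by the fraction retained and round up.
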